### Hypothesis

We hypothesize the following possibilities: (1) GJS combined with Duolac7S will show more beneficial effects on D-IBS symptoms than either GJS or Duolac7S alone; and (2) after 8 weeks of administration of GJS with Duolac7S, intestinal permeability will be lowered and the proportion of lactic acid bacteria in the intestine will be changed.

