#### Assessment of intestinal permeability

Intestinal permeability reflects the intactness of the intestinal mucosal barrier, which regulates the passive permeation of the luminal contents [25]. It is possible to assess intestinal permeability by evaluating the urinary excretion of lactulose and mannitol given orally [26]. Lactulose is only slightly absorbed and serves as a measure of the mucosal integrity while mannitol is easily absorbed and serves as a measure of the transcellular uptake [27]. The lactulose/mannitol (L/M) test is nontoxic and noninvasive in humans and is a stable measurement that is not affected by gastric emptying, intestinal motility, and renal function [28]. Therefore, the L/M test is a relevant method to measure intestinal permeability in the current trial. An increased ratio of the excretion of lactulose to mannitol suggests increased intestinal permeability [26]. Increased intestinal permeability is reported in various intestinal diseases associated with diarrhea such as leaky gut syndrome [25] or IBS [29,30].

The evaluation procedure is as follows: after an overnight fast, each subject will void to empty his or her bladder and then ingest 13.9 g of lactulose together with 5.3 g of mannitol dissolved in 500 mL of water. Urine will be collected over the next 8 h in plastic bags. Patients will drink approximately 2 L of water during the test, and other foods or liquid will not be allowed. The entire urine volume will be measured for 8 h and a 45-mL urine sample will be stored at -70°C until assayed. The urine will be collected at the baseline (week 0) and at the end of the administration (week 8) period.

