#### Pattern analysis of intestinal microbiota

Associations have been observed between IBS patients' symptoms and the presence or quantities of certain gastrointestinal bacteria [31]. In the current study, we will focus on the change in the composition of the intestinal microbiota after administration of the study agents. Each subject will be expected to submit 5 g of fecal samples for bacteriological studies at the baseline (week 0) and at the end of the administration (week 8) periods. The samples will be collected immediately before urine collection and stored at -70°C prior to analysis. The fecal samples will be analyzed in a qualified laboratory (Cell Biotech Co., Ltd., Seoul, Korea) by the denaturing gradient gel electrophoresis (DGGE) method and real-time polymerase chain reaction (RT-PCR), which is a useful genotypic technique for detecting changes in the microbiota [32].

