### Statistical analysis

Statistical analysis of all data will be performed by a specialized statistician in a blind manner. To assess the efficacy of this trial, both the *intention-to-treat *and *per-protocol *populations will be analyzed. Baseline characteristics will be compared by Pearson's chi-square test and analysis of variance (ANOVA). The target variables for analysis in this study include the following: (1) AR and proportion of responders (primary outcomes); (2) VAS for abdominal pain and diarrhea; (3) bowel function scores (frequency, consistency, and ease of passage); (4) severity of individual symptoms (abdominal pain, abdominal discomfort, bloating, flatulence, urgency, and mucus in the stool) and overall symptoms; and (5) IBS-Qol. All values will be presented as mean ± SEM. Comparison between the 4 groups will be performed on the basis of repeated measure ANOVA, and the paired *t*-test will be used to compare between the baseline and after a certain period in each group. The analysis for characteristics such as gender and age between groups will be conducted along with Pearson's chi-square test. All statistical analyses of the data will be performed using the SPSS program, version 16.0 (SPSS Inc., Chicago, IL) and a *P *value < 0.05 will be considered statistically significant.

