## Discussion

Herbal medicine has been considered safe and effective for various diseases based on clinical experiences accumulated for thousands of years in traditional medicine and has gained attention as an alternative treatment for hard-to-cure or cryptogenic diseases such as IBS [33,34]. Despite recent enthusiasm for herbal medicine, there are only few well-designed randomized controlled trials related to herbal medicine, and its mechanisms have been poorly understood. In the current study, we will evaluate the efficacy of GJS, a representative herbal formula that has long been used for managing diarrhea and abdominal pain in traditional Korean medicine [9-11]. In addition, we will evaluate intestinal permeability and the composition of intestinal microbiota as biomarkers to assess the efficacy of GJS. The results of these markers are expected to make it possible to analyze the mechanisms and build up scientific evidences of GJS.

In addition to frequent usage as an herbal formula for IBS, probiotics are one of the promising agents extensively used for IBS. Probiotics have shown effects on IBS through a variety of mechanisms like competing with pathogens for nutrients and receptors, inducing hydrolysis of toxins and receptors, inducing production of organic acids, and modulating nitric oxide synthesis [35]. One notable mechanism of probiotics is the anti-inflammatory effect [36]. Approximately 15% of IBS patients may have a persistent mild inflammatory state resulting in increased intestinal mucosal permeability [37]. The following anti-inflammatory effects of single strains have been reported: *Lactobacillus plantarum *demonstrates significant benefits by increasing interleukin 10 synthesis and secretion in macrophages and T cells derived from the inflamed colon [38]; and *Bifidobacterium breve *and *Streptococcus thermophilus *release metabolites that exert an anti-tumor necrosis factor-alpha effect capable of crossing the intestinal barrier [39]. Duolac7S, a study agent in the current trial, contains these types of bacterial species and is expected to have an anti-inflammatory effect that will improve intestinal permeability.

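### Within-arm paired t-tests at P < 0.05 are planned without being marked descriptive, and hypothesis 2 is worded as a one-arm change with no comparator

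*Protocol article*

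**What the plan says.** The Statistical analysis section of the protocol article introduces its analysis populations with the words "To assess the efficacy of this trial, both the", naming the intention-to-treat and per-protocol populations. It then plans two kinds of test in one sentence:

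- Between arms: "Comparison between the 4 groups will be performed on the basis of repeated measure ANOVA".
- Within arms: a paired t-test that "will be used to compare between the baseline and after a certain period in each group".

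The section closes by applying P < 0.05 to all analyses. It does not say which of the two tests carries the conclusion.

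The Hypothesis section words its two parts differently. The first is a comparison between arms: "GJS combined with Duolac7S will show more beneficial effects on D-IBS symptoms than either GJS or Duolac7S alone". The second is a change over time in one arm: "after 8 weeks of administration of GJS with Duolac7S, intestinal permeability will be lowered", followed by an expected change in the proportion of lactic acid bacteria. No comparator is named in the second part.

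The measurements behind hypothesis 2 have fixed times. For permeability, "The urine will be collected at the baseline (week 0) and at the end of the administration (week 8) period". Stool samples are taken "at the baseline (week 0) and at the end of the administration (week 8) periods". Both are asked of each subject, so also of the double-placebo arm described under Design. The Discussion gives these measures an efficacy role: "we will evaluate intestinal permeability and the composition of intestinal microbiota as biomarkers to assess the efficacy of GJS".

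**The concern.** A before/after change inside one arm is the sum of any treatment effect, the placebo response, the natural course and regression to the mean. The Inclusion criteria require consistent abdominal pain and discomfort, so patients enter while symptomatic and some improvement is plausible in every arm. A paired test in the combination arm cannot divide that sum into its parts. Setting the arms side by side by whether each reached P < 0.05 does not repair this, because a difference between two significance verdicts is not a test of the difference between arms.

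The text leaves room for such a reading. The paired tests stand in the efficacy analysis with their own threshold, and hypothesis 2 could be declared confirmed from the combination arm alone.

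For some outcomes the later time is also open. Diary scores run through run-in, administration and follow-up, and IBS-QoL has two visits after baseline (weeks 8 and 10). The plan does not say which of these the paired test uses.

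**Working it through.** **The plan's own figure.** Sample size calculation gives 12 completers per arm, 20% drop-out and four arms: 12 / (1 − 0.20) = 15 per arm, and 15 × 4 = 60. This reproduces. The stated 80% power cannot be checked, since no effect size, SD or response rate is given.

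**Inputs.** n = 12 (completers) or 15 (randomised) per arm, from Sample size calculation. Alpha is 0.05, from Statistical analysis; two-sided is assumed because sidedness is not stated. The documents give no placebo response or SD, so the mean change divided by the SD of the change (dz) is an assumption, varied from 0 to 1.0. It is set equal in all four arms, so the true drug effect is zero. The calculation concerns continuous outcomes.

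**Formulas.** Probability that one arm's paired test is significant: p = P(|T| > t(0.975, n − 1)), where T is noncentral t with n − 1 degrees of freedom and noncentrality dz × √n. Example: n = 12 and dz = 0.5 give noncentrality 0.5 × √12 = 1.73 and p = 0.353. Separate randomised arms are independent, so the probability that the combination is significant and double placebo is not is p(1 − p); here 0.353 × 0.647 = 0.228.

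| dz, equal in all arms | p, n = 12 | p(1 − p), n = 12 | p, n = 15 | p(1 − p), n = 15 |
|---|---|---|---|---|
| 0 | 0.050 | 0.048 | 0.050 | 0.048 |
| 0.3 | 0.158 | 0.133 | 0.192 | 0.155 |
| 0.5 | 0.353 | 0.228 | 0.438 | 0.246 |
| 0.6 | 0.475 | 0.249 | 0.580 | 0.244 |
| 0.8 | 0.714 | 0.204 | 0.821 | 0.147 |
| 1.0 | 0.883 | 0.103 | 0.949 | 0.048 |

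**Any active arm.** The chance that at least one of the three active arms is significant is 1 − (1 − p)³. At n = 12 this is 40% (dz 0.3), 1 − 0.647³ = 73% (dz 0.5) and 98% (dz 0.8).

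**Open time point, diary outcomes only.** Suppose there is no change at all and any of the 8 treatment weeks may serve as the later time. A simulation of 20,000 runs at n = 12, with assumed equal correlation of 0.5 or 0.7 between occasions, gives a significant week in a given arm with probability about 26%, against 5% for one fixed week. If the eight tests were independent it would be 1 − 0.95⁸ = 34%.

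**Contrast with a between-arm test.** If all arms change equally, the expected difference in change between two arms is zero. One pre-specified between-arm contrast at a fixed time therefore keeps its 5% error rate, whatever the size of the placebo response.

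**The case against.** The best defence is that the plan already contains the right kind of comparison. The paired test shares its sentence with a four-group repeated measures ANOVA, hypothesis 1 is between arms, there is a double-placebo arm, and the sample-size text names superiority over placebo. Paired tests are often reported as background. All of this is true, and it limits the point. Four stronger readings are tempting, and the documents do not support them.

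- A reader might infer that placebo response will be taken for drug effect. The article never says that the paired tests decide efficacy; it only fails to say that they do not. This is a risk, not a stated intention.
- A reader might infer that the mechanism question has no control. Urine and stool are collected from every subject at weeks 0 and 8, so control data will exist. What lacks a comparator is the wording of hypothesis 2. Permeability and microbiota are also absent from the list of target variables, so no test is expressly tied to them. Their times are fixed, so the open time point does not touch them.
- A reader might infer that baseline goes unused in the between-arm test. The article does not say which occasions enter the ANOVA. If baseline is one of them, the group-by-time term compares changes from baseline.
- A reader might take 25% as the typical rate of misleading patterns. It is the ceiling of p(1 − p), reached at p = 0.5. The rate falls to 5% at dz = 0 and to 10% (n = 12) or 5% (n = 15) at dz = 1.0.

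That a condensed article may leave detail to an SAP does not remove the point. The paired test at P < 0.05 and the wording of hypothesis 2 are stated choices, not gaps.

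**Conclusion.** The point holds as one about how inference is worded and ranked, and it should be corrected. The article plans within-arm significance tests that cannot isolate a treatment effect and does not mark them as descriptive. It also states one of its two hypotheses as a one-arm change.

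With zero drug effect and an equal assumed change of 0.3 to 0.8 SD of the change in all arms, a single arm's test is significant with probability 16% to 82% at 12 to 15 per arm. The combination-yes, placebo-no pattern then has probability about 13% to 25%. Over the whole assumed range of 0 to 1.0 SD, that second figure runs from about 5% to 25%.

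These sizes rest on assumed standardised changes, two-sided tests and continuous outcomes. The defect in the wording does not depend on them.

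**What to change.** 1. State in Statistical analysis that conclusions on efficacy and on mechanism rest only on between-arm contrasts.
2. Report within-arm changes descriptively, with estimates and intervals but no P-values.
3. Restate hypothesis 2 as combination versus double placebo, and versus each single agent, in the change from week 0 to week 8 in permeability and lactic acid bacteria.
4. For continuous outcomes, compare arms at a named time with the collected baseline as covariate: the week 0 value for visit measures and the run-in mean for diary scores. Name the time for the diary outcomes, and say whether IBS-QoL is judged at week 8 or week 10.

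The cost is wording. All the data needed are already collected, and the change should be made before the analysis is run. One consequence should be accepted openly: at 80% power a two-arm t-test detects a difference of only about 1.20 SD with 12 per arm, or 1.06 SD with 15, before any baseline adjustment. That imprecision belongs to the sample size, and within-arm tests do not cure it.

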## Discussion

Herbal medicine has been considered safe and effective for various diseases based on clinical experiences accumulated for thousands of years in traditional medicine and has gained attention as an alternative treatment for hard-to-cure or cryptogenic diseases such as IBS [33,34]. Despite recent enthusiasm for herbal medicine, there are only few well-designed randomized controlled trials related to herbal medicine, and its mechanisms have been poorly understood. In the current study, we will evaluate the efficacy of GJS, a representative herbal formula that has long been used for managing diarrhea and abdominal pain in traditional Korean medicine [9-11]. In addition, we will evaluate intestinal permeability and the composition of intestinal microbiota as biomarkers to assess the efficacy of GJS. The results of these markers are expected to make it possible to analyze the mechanisms and build up scientific evidences of GJS.

In addition to frequent usage as an herbal formula for IBS, probiotics are one of the promising agents extensively used for IBS. Probiotics have shown effects on IBS through a variety of mechanisms like competing with pathogens for nutrients and receptors, inducing hydrolysis of toxins and receptors, inducing production of organic acids, and modulating nitric oxide synthesis [35]. One notable mechanism of probiotics is the anti-inflammatory effect [36]. Approximately 15% of IBS patients may have a persistent mild inflammatory state resulting in increased intestinal mucosal permeability [37]. The following anti-inflammatory effects of single strains have been reported: *Lactobacillus plantarum *demonstrates significant benefits by increasing interleukin 10 synthesis and secretion in macrophages and T cells derived from the inflamed colon [38]; and *Bifidobacterium breve *and *Streptococcus thermophilus *release metabolites that exert an anti-tumor necrosis factor-alpha effect capable of crossing the intestinal barrier [39]. Duolac7S, a study agent in the current trial, contains these types of bacterial species and is expected to have an anti-inflammatory effect that will improve intestinal permeability.

Multi-strain probiotics and high-dose probiotics appear to have greater efficacy than single strains and relatively low-dose probiotics [40] and several probiotic mixtures can lead to the improvement of IBS symptoms. A probiotic mixture of 4 bacterial species (5 × 10^9 ^CFU per day) reduced abdominal pain and distension [41]. The probiotic VSL#3, which is a combination of 8 bacterial strains (4.5 × 10^9 ^CFU per day), has shown beneficial effects on flatulence and abdominal bloating [20,22]. Compared to previous study agents, Duolac7S contains a relatively high dose (1.0 × 10^10 ^CFU per day) of probiotics and various types of bacterial species (7 bacterial species). Thus, Duolac7S is anticipated to have a greater effect on IBS symptoms than other single strains or low-dose probiotics.

Predominant bowel dysfunctions, including diarrhea and constipation, can be associated with changes in the intestinal bacterial flora. One case-control study reported a lower concentration of bifidobacteria and a higher concentration of enterobacteriaceae in patients with IBS [42]. Another study using PCR-DGGE showed a higher concentration of coliforms in the IBS patients [43]. A study using high-throughput 16S ribosomal RNA sequencing demonstrated greatly reduced numbers of lactobacilli and collinsella in stool samples of IBS patients and an especially low concentration of bifidobacteria in D-IBS compared to controls [44]. Despite the limitations of these previous studies such as differing patient groups and the complexity of the intestinal microbiota, lactobacilli and bifidobacteria appear to be relatively reduced in patients with IBS. Thus, we assume that Duolac7S, which contains a large dose of lactobacilli and bifidobacteria, will modify the patterns of the intestinal microbiota and have a therapeutic effect on IBS symptoms and improve intestinal permeability by strengthening the integrity of the gut barrier.

The current study has several distinctive features. First, to the best of our knowledge, this will be the first trial to investigate the efficacy of GJS and Duolac7S combination therapy on D-IBS. In spite of the beneficial effects of GJS on IBS in traditional medicine, treatment of IBS by GJS has not been evaluated in clinical trials. No studies have targeted Duolac7S, a mixture of 7 lactic acid bacterial species, as a treatment for D-IBS; however, several studies have suggested that the individual bacterial species in Doulac7S and other probiotics mixtures may improve IBS symptoms. Moreover, GJS and Duolac7S combination therapy has never been the subject of a previous study. Thus, it is expected that the present trial will provide evidence for the effective application of GJS and Duolac7S combination therapy in D-IBS. Second, the participants in the current trial will be grouped into 4 arms. Test groups in this study will be divided into 4 arms in order to identify the efficacy of the combination therapy and to compare each treatment's effect. Ultimately, the combination therapy of GJS and Duolac7S are postulated to generate a synergistic effect resulting in greater improvement of D-IBS symptoms than individual GJS or Duolac7S treatment. Third, we will conduct analyses of intestinal permeability and the composition of intestinal microbiota after administration of GJS with Duolac7S. The urine and stool analysis results could provide evidence for the combination treatment and the possible mechanisms might also be investigated.

Although our study has a relatively small sample size for a pilot study, our trial is considered to have creative and challenging characteristics and is expected to play an important role in providing basic clinical data in the field of herbs and probiotics and developing methodology in IBS studies.

### Trial status

The study was conceived and designed in 2010. The first participant was randomized on 25 April 2011. The recruitment of the study is ongoing.

## Abbreviations

ANOVA: analysis of variance; AR: adequate relief; CBC: complete blood count; CRO: clinical research organization; CRP: C-reactive protein; DGGE: denaturing gradient gel electrophoresis; D-IBS: diarrhea-predominant irritable bowel syndrome; DUO: Duolac7S; DUO-P: placebo of Duolac7S; GJG: Gwakjungsan granule^®^; GJS: *Gwakhyangjeonggisan*; GJS-P: placebo of *Gwakhyangjeonggisan*; IBS: irritable bowel syndrome; IBS-QoL: a quality of life measurement for persons with irritable bowel syndrome; IRBs: institutional review boards; RT-PCR: real-time polymerase chain reaction; VAS: visual analog scale.
